**Methods:**

This prospective, single-center observational cohort study is embedded within the Rheumatoid Arthritis DMARD Tapering (ROADMAP) clinic at Freeman Hospital, Newcastle upon Tyne, United Kingdom. Adults with clinician-confirmed RA in remission who are undergoing or are about to begin DMARD tapering will be recruited, with a target sample of 100 participants. Participants will be followed for 12 months, with clinical assessments aligned with routine ROADMAP visits at baseline and approximately months 3, 6, 9, and 12 together with ad hoc visits for suspected flare. Continuous wrist-worn accelerometry and weekly RA-FQ responses will be collected throughout follow-up. Clinical assessments will include tender and swollen joint counts, patient and physician visual analog scales, C-reactive protein, the DAS28-CRP, and Health Assessment Questionnaire Disability Index scores. The primary outcome is time to first clinically confirmed flare, defined as DAS28-CRP≥2.4 and/or at least 1 swollen joint attributable to inflammatory RA activity. Dynamic risk prediction methods, such as landmarking models, will use longitudinal accelerometry-derived physical activity, mobility, gait, and sleep measures to estimate flare risk over prespecified prediction horizons. Model performance will be assessed using time-dependent discrimination, calibration, predictive values, and lead time before clinically confirmed flare.

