## Introduction

Rheumatoid arthritis (RA) is a common disease affecting approximately 1 in 100 adults in the United Kingdom [1] and is characterized by joint pain and swelling and general features such as fatigue [2]. Patients with RA are prescribed disease-modifying antirheumatic drugs (DMARDs) in order to prevent joint damage and improve symptoms [3]. With modern treat-to-target DMARD regimens, approximately two-thirds of patients newly diagnosed with RA can now achieve disease remission. Once remission is achieved, international clinical guidelines now endorse the gradual reduction (tapering) of DMARDs to reduce the risk of drug side effects and toxicity, reduce medication burden for patients, and reduce drug prescription costs.

The Rheumatoid Arthritis DMARD Tapering (ROADMAP) service was established in early 2023 at Newcastle Hospitals to support a consistent, standardized approach to DMARD tapering for patients with RA seen in rheumatology outpatient clinics [4]. Patients may enter the service while receiving either a full therapeutic dose or a previously reduced but stable dose; therefore, enrollment in this service is not restricted to patients beginning their first tapering step. Tapering is individualized according to DMARD class, current dose, duration of remission, previous tapering history, and clinical judgment. Dose reductions are generally introduced stepwise at approximately 3-month intervals rather than through an immediate reduction (eg, to 50% of the original dose) [4]. At each visit, the current dose, proportion of the reference therapeutic dose, date and magnitude of the most recent reduction, and planned next tapering step are recorded. If flare occurs, treatment is returned to the previously effective dose, with short-term bridging glucocorticoids used when clinically indicated.

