#### Month 3 Visit (±1 Week)

At the week 12 visit, within a 1-week window, patients will be asked to verbally confirm their willingness to continue in the study, and any changes in concurrent medications and any adverse events (AEs) since the last clinic visit will be recorded. A researcher will then assess the 28-joint tender and swollen counts, patient visual analog scale, and physician visual analog scale required for DAS28-CRP disease activity assessment. The patient will complete an HAQ-DI questionnaire and an RA-FQ paper questionnaire, unless an online RA-FQ has already been completed within the previous 24 hours. Any paper questionnaires provided at the last visit and the Axivity AX6 devices from the previous study visit will be collected. If arthritis flare is confirmed, defined as a DAS28-CRP of at least 2.4 or at least 1 swollen joint, this will already have been treated appropriately during the concurrent ROADMAP clinic appointment, and the study investigator will record the patient’s estimated date of flare onset.

All patients will then be offered enrollment in the optional 12-week extension study. If the patient agrees, they will immediately enter the extension phase, be provided with 3 new Axivity AX6 devices and 1 wrist strap to wear for 28 days each in sequence on the nondominant wrist, or the dominant wrist if needed, and, if they are unable to access the online REDCap portal, they will also be given 12 additional paper RA-FQs to complete weekly; their next and final study visit will take place 12 weeks later, 84 days, according to schedule 6.3. If the patient declines the optional extension, they will exit the study at this visit and will be given a feedback questionnaire on the usability and acceptability of the AX6 devices together with a stamped addressed envelope for postal return to the study team.

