If arthritis flare is confirmed, defined as a DAS28-CRP of at least 2.4 or at least 1 swollen joint, this will already have been treated appropriately during the concurrent ROADMAP clinic appointment. The study investigator will record the estimated date of flare onset, and follow-up in the main study period will be terminated if not already completed. Patients who are not already enrolled in the optional 12-week extension study will be offered enrollment. If they agree, they will immediately enter the extension phase, any paper questionnaires and Axivity AX6 devices from the last visit will be collected, and they will be provided with 3 new Axivity AX6 devices and 1 wrist strap to wear for 28 days each in sequence on the nondominant wrist, or the dominant wrist if needed. If they cannot access the online REDCap portal, they will also be given 12 additional paper RA-FQs to complete weekly, and their next study visit will take place in 12 weeks according to schedule 6.3, replacing the planned week 12 main study visit. If the patient is already enrolled in the optional extension study, they will be given a feedback questionnaire on AX6 usability and acceptability, will continue wearing the AX6 monitors and completing any provided paper RA-FQs for the remainder of the ongoing 12-week extension period, and will then exit the study without an extension week 12 review to avoid an extra visit outside the ROADMAP clinic schedule; they will also be given a stamped addressed envelope to return the AX6 monitors and paper questionnaires by post. If a patient with confirmed flare declines the optional extension study, they will exit the study at that visit, any paper questionnaires and AX6 devices from the last visit will be collected, and they will be given a feedback questionnaire on AX6 usability and acceptability together with a stamped addressed envelope for postal return to the study team. If arthritis flare is not confirmed, the patient will continue to wear the Axivity AX6 monitors and complete RA-FQs according to the current schedule and will attend the next study visit as already arranged.

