### Primary Analyses

The primary outcome is the time from study enrollment to the first clinically confirmed RA flare, defined as a DAS28-CRP of 2.4 or above.

The primary objective of the study is to predict clinically confirmed flare risk using dynamic risk prediction methods based on daily accelerometry data including both the quality metrics and the physical activity measures. In addition, we would like to retrospectively assess the accuracy of the model vs patient-reported flare.

We will use landmarking models to develop a dynamic risk prediction approach for arthritis flare. Landmarking is a time-updated survival modeling framework that generates risk predictions at predefined time points (landmark times) using information available up to each time point. Predictions are then made over specified future time horizons.

The approach consists of two components:

A longitudinal submodel, which summarizes repeated accelerometry-derived measurements over timeA time-to-event submodel, which estimates the risk of flare from each landmark time

At each landmark time, the longitudinal submodel is used to extract summary measures of the accelerometry data up to that time, and these summaries are then included as predictors in the time-to-event model to estimate the future risk of flare.

The event of interest is the first clinically confirmed arthritis flare. Participants who do not experience a clinically confirmed flare will be censored at the end of their individual follow-up period or at earlier withdrawal.

For the time-to-event component, we will fit both Cox proportional hazards models and random survival forests (RSFs) to assess potential improvements in predictive performance and capture potential nonlinear relationships and interactions. We also consider including variables such as age, sex, Clinical Frailty Score, and anticitrullinated protein antibodies (ACPAs) antibody status (either positive/negative or the actual titer) as fixed effects or variables in both longitudinal and time-to-event submodels as they are clinically important.

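### The primary event is defined in two ways: read literally, Primary Analyses needs DAS28-CRP of 2.4 or above, while the abstract and visit sections also accept one swollen joint

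*Protocol article*

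**What the plan says.** Five places in the protocol article define the flare.

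- **Primary Analyses** gives this definition: "The primary outcome is the time from study enrollment to the first clinically confirmed RA flare, defined as a DAS28-CRP of 2.4 or above". No swollen-joint criterion appears.
- **Abstract, Methods:** the same primary outcome, time to first clinically confirmed flare, is met by DAS28-CRP of 2.4 or more "and/or at least 1 swollen joint attributable to inflammatory RA activity".
- **Extension Study (months 6, 9 and 12):** clinically confirmed flare has the same composite definition as in the abstract, including attribution to RA.
- **Month 3 Visit:** "If arthritis flare is confirmed, defined as a DAS28-CRP of at least 2.4 or at least 1 swollen joint". The attribution wording is absent.
- **Ad Hoc Flare Visits:** "defined as a DAS28-CRP of at least 2.4 or at least 1 swollen joint, this will already have been treated appropriately". The attribution wording is again absent.

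Later sentences in Primary Analyses call the event the first clinically confirmed arthritis flare, and censor patients who do not have one. The weekly landmark paragraph calls it clinician-defined flare. None of these sentences says which definition applies.

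On management, the Introduction says: "If flare occurs, treatment is returned to the previously effective dose, with short-term bridging glucocorticoids used when clinically indicated". At an ad hoc visit with confirmed flare, "follow-up in the main study period will be terminated if not already completed". A patient already in the extension "will continue wearing the AX6 monitors and completing any provided paper RA-FQs for the remainder of the ongoing 12-week extension period". On evaluation, the abstract says: "Model performance will be assessed using time-dependent discrimination, calibration, predictive values, and lead time before clinically confirmed flare".

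**The concern.** In four of the five places a swollen joint is enough on its own. In the section that governs the primary analysis it is not mentioned. The two event sets differ by patients who have an RA-swollen joint and a DAS28-CRP below 2.4. The clinic confirms and treats these patients as flares, and under the Introduction their dose is restored.

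What is at stake is the target that the model learns and is judged against. An analyst who codes from Primary Analyses would treat an alarm shortly before such a flare as a false positive. The follow-up after dose restoration would count as flare-free time, or the patient would be censored for a reason tied to flare. The event set, the observed event rate and the predictive values would then depend on which section the analyst had read.

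**Working it through.** **1. One patient under each definition.** Take a patient with a swollen joint attributed to RA and a DAS28-CRP below 2.4.

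- Composite definition: this is an event. Time at risk ends, and the two weekly landmarks in the preceding 14 days are positive.
- DAS28-only definition: there is no event, and those two landmarks are negative. If the patient declines the extension and leaves, they are censored because of the flare. If they enter the extension, or are already in it, monitoring continues and they stay at risk as flare-free after treatment.

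**2. Illustrative size.**

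Inputs from the document:
- 100 patients and a 50% flare rate (Target Recruitment Sample Size)
- a maximum of 6 months of follow-up under the current approval, taken as 24 weeks (Ethical Considerations)
- weekly landmarks and a 14-day horizon (Primary Analyses)

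Assumptions, because the document gives no figure:
- the 50% is the composite rate over those 24 weeks
- flares are evenly spread, at a mean of 12 weeks
- y of the 50 flares are swollen-joint only, with y = 1, 5 or 10
- none of these y patients later reaches DAS28-CRP of 2.4

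Composite definition: landmarks = 50×24 + 50×12 = 1800; positives = 50×2 = 100; rate = 100/1800 = 5.56%.

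Extra landmarks per uncounted flare: half of the flares fall in the first 12 weeks. Those patients add 0 landmarks if they leave, or 12 if they start a new 12-week extension. The other half fall in the extension and add the remainder, 6 weeks on average. The mean therefore lies between 0.5×0 + 0.5×6 = 3 and 0.5×12 + 0.5×6 = 9.

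DAS28-only rate = (100 − 2y)/(1800 + 3y) to (100 − 2y)/(1800 + 9y).

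| y | Events | Positives relabelled | Rate | Relative fall |
|---|---|---|---|---|
| 1 | 49 | 2 of 100 | 98/1803 = 5.44% to 98/1809 = 5.42% | 2.2-2.5% |
| 5 | 45 | 10 of 100 | 90/1815 = 4.96% to 90/1845 = 4.88% | 10.7-12.2% |
| 10 | 40 | 20 of 100 | 80/1830 = 4.37% to 80/1890 = 4.23% | 21.3-23.8% |

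**3. Discrimination.** Let the true pooled AUC be 0.80. Relabelled landmarks look like true positives, so they compare at 0.5 with the remaining positives. All other negatives compare at 0.8. With the lower landmark totals:

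- y = 1: (1703×0.8 + 2×0.5)/1705 = 0.800
- y = 5: (1715×0.8 + 10×0.5)/1725 = 0.798
- y = 10: (1730×0.8 + 20×0.5)/1750 = 0.797

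The higher totals give the same three decimals.

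**4. Sample size.** The plan's figure is 100 patients for 90% power, with AUC 0.8 against 0.6 and two-sided 0.025. Power = Φ[(0.2 − z·SE0)/SE1], with z = 2.24 and SE0 taken under the null AUC. At 50 events, Hanley-McNeil gives SE0 = 0.0566, SE1 = 0.0445 and power 95.0%; the Obuchowski variance gives 93.7%. These forms reach 90% power at 86 and 90 patients, so 100 is sufficient on the stated inputs. At 40 events (y = 10), power is 92.7% or 92.1%. It drops below 90% only when fewer than about 35% of patients have an event.

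**The case against.** The strongest reply is that the sentence in Primary Analyses is shorthand. The event and censoring sentences that follow it speak of a clinically confirmed flare, and the extension section defines that term as the composite. On that reading a treated swollen-joint patient is an event and is not kept at risk. The short definition cannot be fully literal in any case, because the Clinical Discretion section lets the investigator discount a raised DAS28-CRP caused by infection or trauma. This stands as far as it goes. A reader might infer that the plan definitely excludes swollen-joint flares, but the document supports only an unresolved ambiguity. Still, Primary Analyses attaches its own explicit definition to the term, so the shorthand reading is not secured either.

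Three other inferences go too far.

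- **Miscalibration.** A model built and tested on the DAS28-only event has a different target. It is not thereby miscalibrated.
- **A stated loss of positive predictive value.** A number would need a fixed alarm threshold and an assumption that these flares are flagged as often as others. The article gives no threshold, so I put no figure on it.
- **Non-RA swelling counted as flare at the month 3 and ad hoc visits.** Clinical Discretion already covers swelling from trauma and expects agreement with the clinic. Its text is framed around a raised DAS28-CRP, so shared attribution wording would be tidier, but the substance is there.

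It is also fair to say that this is a development phase sized on AUC, and AUC hardly responds.

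**Conclusion.** The inconsistency is certain: current text gives the same primary outcome two definitions, and nothing in the article reconciles them. The consequence is conditional on an analyst following Primary Analyses literally. In that case the event set, the observed event rate and the predictive values change.

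The relative falls in event rate, from about 2% to 24%, are illustrations. They rest on assumed counts of 1 to 10 swollen-joint-only flares, on reading the 50% as a composite rate over 24 weeks, on an even spread, and on no later DAS28-CRP event in these patients. The sample-size paragraph gives neither the flare definition nor the time frame behind its 50%. A reader might infer that the AUC test or its power is in danger, but over the range shown AUC stays at 0.797 or above and power above 90%. This is a cheap improvement to the primary endpoint's wording.

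**What to change.** - In Primary Analyses, replace the DAS28-only definition with the composite used in the abstract and the extension section: DAS28-CRP of 2.4 or more, and/or one or more swollen joints due to inflammatory RA.
- Use the same attribution wording in the month 3 and ad hoc sections, in line with Clinical Discretion.
- Use one name for this event in the outcome, censoring and landmark sentences. The censoring rule itself then needs no change.
- The inclusion criteria admit patients on DAS28-CRP below 2.4 alone. State that an RA-swollen joint already present at baseline is not a day-0 event.
- If wanted, keep the DAS28-only event as a sensitivity analysis.

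The cost is wording only. Swollen joints are already counted at every visit. By 1 July 2026, 16 patients had been recruited, and the main analysis waits for complete follow-up, so the definition can be settled before any outcome analysis. The downside is that the swollen-joint part relies on the investigator's attribution to RA.

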#### Extension Study: Months 6, 9, and 12 Visits (±1 Week)—If Participating in Optional Extension Study

Participants entering the optional extension may attend follow-up visits at month 6 (week 24 ±1 wk), month 9 (week 36 ±1 wk), and month 12 (week 52 ±1 wk). At the month 6 and month 9 visits, participants will verbally confirm their willingness to continue. Changes in concurrent medications and any AEs since the previous visit will be recorded at each visit. A researcher will assess the 28-joint tender and swollen joint counts and the patient and physician visual analog scales. CRP results obtained through routine clinical care will also be recorded to calculate the DAS28-CRP. Participants will complete the HAQ-DI and a paper RA-FQ unless they have completed the online RA-FQ within the preceding 24 hours.

A clinically confirmed flare will be defined as a DAS28-CRP of ≥2.4 and/or at least 1 swollen joint attributable to inflammatory RA activity. Confirmed flares will be managed by the ROADMAP clinical team as part of routine care, and the study investigator will record the estimated date of flare onset. At each visit, completed paper questionnaires and Axivity AX6 devices from the preceding monitoring period will be collected. Participants who do not wish to continue at month 6 or month 9 will complete the wearable usability and acceptability questionnaire and exit the study. All participants remaining in the study at month 12 will complete the questionnaire and exit the study. No participant will be followed for more than 12 months from baseline. These optional extension visits will be implemented only after approval of the submitted ethics amendment and all required sponsor and site approvals.

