### Clinical Discretion

It is possible for DAS28-CRP scores to be elevated by events unrelated to inflammatory arthritis: for example, by a concurrent infection causing an elevation of CRP, or trauma causing a painful or swollen joint. The study investigator has discretion to discount such false elevations of the DAS28-CRP and follow the remission section for the relevant study visit if felt to be appropriate. In such cases, it is expected that the study investigator’s decision should match that of the ROADMAP service clinician; for example, if a patient with concurrent infection had an elevated DAS28-CRP, but the ROADMAP clinician considered their arthritis to still be in remission, then the study investigator should manage the patient as being in remission.

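### Entry and flare share the DAS28-CRP cut-off of 2.4 with no minimum rise, so flare status depends partly on entry level and accelerometry could be credited with it

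*Protocol article*

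**What the plan says.** Textbox 2 (inclusion criteria) admits patients with a DAS28-CRP below 2.4 at enrollment. It sets no margin below that value.

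Primary Analyses takes as outcome the time from enrollment to the "first clinically confirmed RA flare, defined as a DAS28-CRP of 2.4 or above". Other sections word the event more widely. The abstract has "defined as DAS28-CRP≥2.4 and/or at least 1 swollen joint attributable to inflammatory RA activity", and the extension-visit section agrees with it. The Month 3 Visit section has "If arthritis flare is confirmed, defined as a DAS28-CRP of at least 2.4 or at least 1 swollen joint", without the attribution clause. The DAS28-CRP limb is the same in all of them: a score at or above 2.4 at a visit. No section asks for a minimum increase from the participant's own baseline or for a second reading.

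The Clinical Discretion section provides a safeguard: "The study investigator has discretion to discount such false elevations of the DAS28-CRP". Its stated scope is that "It is possible for DAS28-CRP scores to be elevated by events unrelated to inflammatory arthritis", with examples: "for example, by a concurrent infection causing an elevation of CRP, or trauma causing a painful or swollen joint". The investigator's decision is expected to match that of the service clinician.

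Baseline DAS28-CRP components are recorded for everyone (Baseline Visit). The covariates that Primary Analyses names as candidates are age, sex, Clinical Frailty Score and ACPA status. The list is introduced as examples, so baseline DAS28-CRP is unnamed rather than excluded.

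**The concern.** Because the event threshold is the entry threshold turned round, a patient who moves from 2.35 to 2.45 is a flare, while one who moves from 1.2 to 2.3 is not. Two problems follow for a prediction study.

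First, measurement variation in the visual analog scale, tender joint count or CRP can carry a stable patient over the line. The rule is applied at each scheduled visit and at any ad hoc visit, and the first crossing counts, so chances accumulate.

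Second, whether a participant becomes an event depends on how close to 2.4 they started. The Introduction reports, from a pilot of 11 patients with active RA, strong correlations between accelerometry outcomes and disease activity indicators. A model could therefore discriminate partly by sorting patients on entry level rather than by seeing change before a flare. The study aims to show that accelerometry detects flare, and the AUC as planned would not separate the two.

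**Working it through.** **The plan's own figure.** Target Recruitment Sample Size gives H0 AUC ≤0.6, true AUC 0.8, 50% flare rate, two-sided alpha 0.025, 90% power and N = 100. With the Hanley-McNeil variance and 50 events against 50 non-events, the SE is 0.0566 at AUC 0.6 and 0.0445 at 0.8. Then z = (0.20 − 2.241 × 0.0566)/0.0445 = 1.64, which is 95% power. Ninety percent power needs N = 86 (N = 90 with the Obuchowski variance, where N = 100 gives 93.7%). So 100 is sufficient on these inputs, though not reproduced exactly.

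**One stable patient.** With true level t and visit SD s, the chance of a score ≥2.4 at one visit is p = 1 − Φ((2.4 − t)/s), and over k visits it is 1 − (1 − p)^k. Both t and s are assumptions. With s = 0.3:

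| True level | 1 visit | 2 visits | 4 visits |
|---|---|---|---|
| 1.8 | 2.3% | 4.5% | 8.8% |
| 2.2 | 25% | 44% | 69% |

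**A stable cohort.** Simulation of 400,000 patients per scenario: true level ~ N(mean, 0.3²), baseline and follow-up readings = true level + N(0, SD²), enrolled if baseline <2.4, event if any follow-up reading ≥2.4, no true change. The mean, between-patient SD and visit SD are all assumed. Two visits correspond to the approved 6 months (Ethical Considerations), four to the 12-month schedule. The table gives the percentage crossing over 2 / 4 visits.

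| Visit SD | Mean 1.5 | Mean 1.7 | Mean 1.9 |
|---|---|---|---|
| 0.2 | 0.9 / 1.5 | 3.2 / 5.3 | 8.7 / 13.6 |
| 0.3 | 2.7 / 4.9 | 7.2 / 12.1 | 15.3 / 24.5 |
| 0.4 | 6.0 / 10.7 | 12.5 / 21.3 | 22.5 / 35.9 |
| 0.5 | 10.4 / 18.5 | 18.3 / 30.9 | 29.0 / 45.8 |

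**Dependence on entry level.** At mean 1.7 and SD 0.3 over four visits, 33% of stable patients who entered above 2.1 cross, against 5% of those who entered below 1.8. Across the grid, the entry reading alone ranks stable crossers against non-crossers with an AUC of about 0.62 to 0.93 over four visits.

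**A mixed cohort.** Give half the patients a true rise of 0.8 (assumed) and leave the rest stable, with mean 1.7 and four visits. Entry DAS28-CRP alone then discriminates recorded events with an AUC of about 0.63 (SD 0.3) and 0.61 (SD 0.4). Over the whole grid it runs from 0.59 to 0.71. The null value in the sample-size section is 0.6.

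**The opposite direction.** If a share f of recorded flares is noise that the model cannot rank at all, AUC = 0.8(1 − f) + 0.5f = 0.8 − 0.3f. With f = 10% this is 0.77 and power at N = 100 is 82%. With f = 20% it is 0.74 and power is 60%.

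**What a minimum rise does.** With 0.6 used purely as an illustration (mean 1.7, four visits), requiring that rise as well takes the stable crossings from 12.1% to 5.9% at SD 0.3, and from 21.3% to 14.3% at SD 0.4. It also drops recorded crossings among patients with a true 0.8 rise: about 14–15% at a single visit, 9% over two and 5% over four.

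**The case against.** The strongest reply is that the event is not a bare number. The abstract and extension section add a swollen joint attributable to RA, Primary Analyses also speaks of clinician-defined flare, and the investigator may overrule the score in line with the service clinician. That stands. A reader might infer that clinical confirmation means nothing more than one reading; the documents do not support that. What remains is that the discretion is worded for causes unrelated to inflammatory arthritis, and the attribution clause reads most naturally with the swollen joint. Neither clearly reaches ordinary variation in a DAS28-CRP-only crossing.

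A reader might also infer that noise alone will turn stable patients into a material share of primary events. That is a statement of size that the documents cannot bear, since they give no within-patient SD and no baseline distribution. The simulation also contains no clinician and no swollen-joint limb. Four visits per patient is a ceiling: continuing past month 3 is optional, and follow-up beyond 6 months awaits ethics approval.

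A third tempting reading is that the AUC will fall to about 0.75–0.77. That assumes noise crossings are unpredictable, yet entry level predicts them. It also adds them on top of a 50% flare rate that draws partly on clinic outcomes and may already include such crossings. The direction is not established.

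Finally, loss of remission is a coherent endpoint for a pilot. The secondary refit on patient-reported flare tests robustness to another definition of flare, but it does not examine this threshold or baseline closeness to it.

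**Conclusion.** The point holds in a limited form. The DAS28-CRP limb of the primary event is the exact complement of the entry criterion, without a minimum rise or repeat measurement, so some stable patients who enter near 2.4 can be recorded as flares and event status depends partly on entry level. The share of stable patients affected is unknown: about 1.5% to 46% over four visits and about 1% to 29% over two, on assumed means of 1.5–1.9, between-patient SD 0.3 and visit SDs of 0.2–0.5. The net effect on the AUC may be up or down.

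The consequence that matters most is interpretive. Under the assumed mixed cohort, entry level alone comes close to or passes the 0.6 cut-point, so an AUC above 0.6 would not by itself show that accelerometry detected change. How far accelerometry tracks entry level in patients in remission is also not known from the documents. This merits a change to the analysis, not a new primary definition.

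**What to change.** 1. In Primary Analyses, name baseline DAS28-CRP as a covariate in both the Cox and random survival forest models. Report accelerometry performance as the gain over a model holding only baseline DAS28-CRP and the other baseline covariates. The benchmark is essential: adding the covariate alone can raise the overall AUC precisely because the model then uses closeness to 2.4.

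2. Keep the current definition as primary. Prespecify one sensitivity analysis in which a DAS28-CRP-only crossing counts only if it also exceeds the participant's baseline by a minimum amount, fixed by the sponsor before data lock. An event that rests on an attributable swollen joint, as worded in the extension-visit section ("DAS28-CRP of ≥2.4 and/or at least 1 swollen joint attributable to inflammatory RA activity"), would be untouched by this. Because Primary Analyses omits the swollen-joint limb that other sections include, those passages must be reconciled first.

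Cost: one more parameter in a small sample, a baseline-only fit and one extra model run. No new visits or data are needed, and with 16 of 100 participants recruited by July 1, 2026, the change can be made before any outcome analysis. The minimum-rise analysis will have fewer events, miss some small true rises and remove only part of the noise crossings, which is why it belongs as a sensitivity analysis. Clinical handling of flare is unaffected.
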